### Statistical analysis plan

Baseline characteristics of study participants will be summarised using percentages or means and SD as appropriate and compared using t tests for continuous variables (expressed as mean±SD) and the χ^2^ tests or the Fisher’s exact tests for categorical variables (expressed as count and percentage). Secondary endpoints for intervention and control groups will be compared using χ^2^ test for binary outcomes, and t-test for continuous outcomes. For subgroup analyses, linear or logistic regression will be used to determine the effects of treatment allocation according to HF status. No adjustment or imputation will be used for missing data. For this feasibility study, we considered a sample of 20 participants enrolled as a minimum number acceptable for feasibility and a daily mean difference of 250 mL of fluid intake between treatment arms as clinically relevant. Progression to a multicentre clinical outcomes trial will be contingent on a series of stop/go criteria based on achieving the primary outcome targets and on secondary outcomes relating to data quality.

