### Randomisation and blinding

Subjects will be randomised 1:1 using an internal random number rule implemented using a standard EPIC randomisation tool used in other PCTs.^25^ No block randomisation or additional covariate balancing will be undertaken. The study is open label with patients and their care teams being made aware of the treatment allocation.

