#### Secondary outcomes

Adherence to randomised treatment recommendation.Proportion of alerts resulting in clinical orders for nursing care.Oral fluid intake.Net fluid balance.Weight change after randomisation.Length of stay.Frequency of blood test measurements of renal function.Prescription of diuretic medications.Daily change in creatinine.Patient-reported outcome measures.

These outcomes were chosen based on clinical relevance and the ability to detect the possibility of attributable harm during an inpatient admission.

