### Data collection, curation and storage

Baseline characteristics and study outcomes will be extracted from the routine care record. Information on the frequency of the interruptive alert and staff responses to alerts will be recorded in EPIC. We will also extract primary and secondary International Classification of Diseases (ICD)-10 diagnosis codes assigned to the clinical episode by the clinical coding team. Study data will be transferred to a secure research environment within UCLH NHS Foundation Trust as pseudoanonymised electronic case report forms (eCRFs). No data will leave the UCLH NHS system. Patients who opt out or withdraw from the trial will have their decision documented on the eCRF and their data will not be included in the main analysis.

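### Weight and creatinine change are compared by unadjusted t-test, and randomised baseline characteristics are significance-tested; adjust for the baseline value and drop the baseline p-values (minor)

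*Protocol article*

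**What the plan says.** All references are to the protocol article.

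- **Statistical analysis plan, secondary endpoints:** "Secondary endpoints for intervention and control groups will be compared using χ^2^ test for binary outcomes, and t-test for continuous outcomes". The method at issue is the "t-test for continuous outcomes". No covariate, transformation or rank-based alternative is named. Regression appears only for subgroup analyses by heart failure (HF) status.
- **Statistical analysis plan, baseline:** characteristics are to be "compared using t tests for continuous variables", with χ² or Fisher's exact tests for categorical ones. Nothing is said about how the resulting p-values would be used.
- **Secondary outcomes:** the list includes weight change, "Daily change in creatinine" and "Length of stay".
- **Randomisation and blinding:** allocation is 1:1 and simple: "No block randomisation or additional covariate balancing will be undertaken".
- **Data collection, curation and storage:** "Baseline characteristics and study outcomes will be extracted from the routine care record".
- **Sample size and power calculation:** the target is 50 patients, with no formal calculation. The Statistical analysis plan sets 20 enrolled as the minimum acceptable for feasibility.

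**The concern.** A change score uses the baseline value, but with a fixed coefficient of 1. When the correlation between baseline and follow-up is below 1, that coefficient is too large. A patient who starts high tends to fall for reasons unrelated to the arm, and an arm that starts higher by chance will seem to improve more. Simple randomisation of 20 to 50 patients makes such starting differences common, and the design does nothing to prevent them. Regression on the baseline value estimates the coefficient from the data, removes this distortion and is usually more precise.

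The baseline significance tests do not fill that gap. Under random allocation any baseline difference is due to chance, so the tests ask a question whose answer is known, and the plan does nothing with the result. They also invite readers to treat a chance p<0.05 as a defect of the randomisation, or p>0.05 as proof of balance.

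At stake are the precision and readability of the secondary estimates that the article says will inform later multicentre trials.

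**Working it through.** The article states no SD, correlation, alpha or power, so there is no figure to reproduce. The values of rho, log-SD and the number of baseline variables below are assumptions, shown as ranges. Two-sided alpha is taken as 0.05.

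**1. Adjusted analysis against t-test on change.** Take one before-and-after pair with equal variance σ² and correlation rho.

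- Variance of change: 2σ²(1−rho). Residual variance after adjustment: σ²(1−rho²).
- Ratio: (1−rho²)/[2(1−rho)] = (1+rho)/2.
- rho 0.5: 0.75 (25% lower). rho 0.7: 0.85 (15% lower). rho 0.9: 0.95 (5% lower).

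Estimating the slope has a price. With a normally distributed covariate, the variance is multiplied on average by 1+1/(N−4).

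- N=50: factor 1+1/46 = 1.022. Ratios become 0.77, 0.87 and 0.97.
- N=20: factor 1+1/16 = 1.063. Ratios become 0.80, 0.90 and 1.01.

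The gain is therefore useful at moderate rho. At rho 0.9 it is small with 50 patients and absent with 20.

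**2. How often baseline imbalance arises.** The SD of the difference in baseline means, in units of the patient SD, is √(2/n).

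- 25 per arm: √(2/25) = 0.283. A gap above 0.3 SD in either direction corresponds to z = 0.3/0.283 = 1.06, probability about 29%.
- 10 per arm: √(2/10) = 0.447, z = 0.67, probability about 50%.

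Given a gap of 0.3 SD, the change-score comparison is shifted by (1−rho)×0.3 SD: 0.15, 0.09 and 0.03 SD at rho 0.5, 0.7 and 0.9.

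**3. Baseline significance tests.** With k independent variables tested at 0.05, the chance of at least one p<0.05 under correct randomisation is 1−0.95^k.

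- k = 5: 23%; k = 10: 40%; k = 15: 54%; k = 20: 64%.

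Correlated variables would give different figures.

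**4. Length of stay.** Simulated log-normal stays, 40,000 replicates, 25 per arm, true ratio 1.5. Power of the raw t-test against the log-scale t-test:

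- log-SD 0.6: 0.58 v 0.65
- log-SD 0.8: 0.33 v 0.42
- log-SD 1.0: 0.20 v 0.29
- log-SD 1.2: 0.13 v 0.22

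The type I error of the raw t-test falls from 0.049 to 0.036 over that range at 25 per arm, and from 0.043 to 0.029 at 10 per arm. The raw t-test is thus conservative and loses power; it does not produce extra false positives.

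**The case against.** The strongest reply is that nothing here is invalid. A change-score comparison is unbiased over repeated randomisations. If repeat inpatient weights are very highly correlated, the gain is slight: 5% at rho 0.9 and 2.5% at 0.95, before the small-sample cost. The formula assumes one before-and-after pair, whereas a daily creatinine change may be a repeated measure. The baseline p-values drive no covariate choice or progression decision. The study claims no power, and its stop/go criteria rest on the primary targets and on data quality. All of this stands, and it is why the point is minor. It does not give a reason to keep the t-test on change, whose only saving is one degree of freedom, or to keep tests that serve no purpose.

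Four stronger readings are tempting, and the article does not support them.

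- *Every continuous outcome gets an unadjusted t-test.* The sentence covers secondary endpoints only. No test is named for the primary difference in oral fluid intake, and regression is planned for subgroups. The sentence ruling out adjustment or imputation concerns missing data, not covariates.
- *Deaths are mishandled in length of stay.* The article does not mention death. That an in-hospital death shortens the stay is a fair inference, but no wrong rule is stated, and the detail may sit in a fuller document.
- *The t-test on skewed stays gives false positives.* The simulation shows the opposite. A log-scale or rank-based analysis also answers a different question from mean days, so changing to one is a trade-off.
- *HF status should be added as a covariate.* The only diagnosis source described is ICD-10 codes assigned to the episode, which may be settled after randomisation. No pre-randomisation value of oral intake is described either, so no gain can be claimed for that outcome.

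**Conclusion.** The point holds for two stated choices: unadjusted t-tests on weight and creatinine change, and significance tests of baseline characteristics. For the first, the large-sample variance penalty is 25%, 15% or 5% of the change-score variance at rho 0.5, 0.7 or 0.9, and there is a conditional shift when arms differ at baseline. For the second, a chance p<0.05 somewhere in the baseline table is more likely than not with 15 independent variables (54%). These sizes rest on assumed correlations, equal variances, a single before-and-after pair and an assumed number of variables, none of which the article gives. For length of stay the issue is efficiency and interpretation only. Severity is minor: the endpoints are secondary, the study is a feasibility trial, and no progression rule is shown to depend on these tests.

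**What to change.** 1. For weight and creatinine, replace the t-test on change with linear regression of the follow-up value on arm and the pre-randomisation value, and report the adjusted difference with a 95% CI. Define the follow-up time. If daily creatinine values are analysed together, keep the same baseline covariate in a repeated-measures model.
2. Delete the between-arm tests of baseline characteristics and give descriptive summaries by arm.
3. As a secondary suggestion, add a log-scale or rank-based sensitivity analysis of length of stay, with any in-hospital deaths reported separately by arm.
4. Use HF status as a covariate only if it is defined from information recorded before randomisation.

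The cost is wording and one degree of freedom. No patient is lost by the adjustment, because a patient without a baseline value already has no change score. The article gives December 2023 as the estimated completion date. If outcome data by arm have already been seen, the adjusted analysis should be labelled as added later and shown beside the planned t-test.

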## Monitoring and evaluation

The trial will report serious adverse events (SAEs) that are attributable to the study through the EHR, in accordance with the safety reporting processes and sponsor policy.^27^ The Trial Management Group will review recruitment rates, SAEs and any substantial amendments to the protocol.

### Ethics and dissemination

This study protocol was approved by the London Riverside Research Ethics Committee (Ref: 22/LO/0889) and sponsored by University College London (Ref: 151938). A verbal opt-out model of consent was adopted based on the negligible risk associated with the intervention. Patients are informed of their study participation and of their treatment allocation and can opt-out of the study or decline to follow the recommendation for oral fluid restriction at any time. A copy of the sample PIS is provided to patients (online supplemental appendix 5). The data management for the trial conforms to NHS Information standards DCB0129 and DCB0160 and was approved by University College London Hospitals NHS Foundation Trust (UCLH) Digital Services Safety board.^30^ The alert is not classified as a separate piece of software but is incorporated within the Epic EHR, which is registered as a class I medical device by the UK Medicines and Healthcare products Regulatory Agency.^31 32^ The study findings will be disseminated through publication in open-access peer-reviewed journals and through the provision of reports for patients and clinicians involved in the study. As a feasibility study, the findings shared will include trial evaluation, and whether alerts which ‘nudge’ clinicians to recruit patients into pragmatic, low-risk comparative effectiveness trials,^33^ are a scalable way to conduct efficient RCTs.^18^ The THIRST Alert feasibility study will share insights that inform the design and execution of future integrated approaches to evidence generation from routine care.
